## 6.9 Drug accountability

### *Fecal microbiota transplantation*

Excipients for the LFMT capsules (trehalose, maltodextrin, sterile saline, silicon dioxide and microcrystalline cellulose, all pharmaceutical grade) will be ordered and handled by the Amsterdam UMC Hospital Pharmacy under supervision of [name], hospital pharmacist at the Amsterdam UMC. In addition, the stomach acid resistant capsules, NGE-caps, will be ordered at Capsugel via the Hospital Pharmacy. Containers will be ordered via the Amsterdam UMC Hospital Pharmacy as well. All excipients and materials will be stored in a dedicated production room for the LFMT capsules at a dry place below 25°C according to prescription by the manufacturer.

The executing researchers will be responsible for the production, storage and dispensing of the LFMT capsules to the respective study subjects, as well as the drug accountability. At the end of the intervention period, any remaining LFMT capsules will be returned by the study subjects to the investigator and will be counted and destroyed by the executive researcher.

### *Anaerobutyricum soehngenii CH106*

Capsulated formulation of *A. soehngenii* CH106 will be delivered by Caelus in small bottles, each containing 50 capsules and a small silicabag to ensure low moisture inside the bottles. The sponsor will be responsible for storing *Anaerobutyricum soehngenii* CH106 in a proper place, inaccessible to unauthorized persons. The sponsor will be responsible for storing pAkk at the appropriate conditions and inaccessible to unauthorized persons.

The investigator agrees that *Anaerobutyricum soehngenii* CH106 will be dispensed only to study participants who have provided written consent. Participants will be instructed to store the product at room temperature (15-25°C), in a dry place away from direct sunlight.

*Bifidobacterium animalis subsp. lactis BLC1*

Capsulated formulation of *B. animalis* subsp. *lactis* BLC1, produced by SynBiotec will be delivered by Caelus. Further details can be provided upon delivery.

The sponsor will be responsible for storing *Bifidobacterium animalis subsp. lactis BLC1* in a proper place, inaccessible to unauthorized persons. The sponsor will be responsible for storing pAkk at the appropriate conditions and inaccessible to unauthorized persons.

The investigator agrees that *Bifidobacterium animalis subsp. lactis BLC1* will be dispensed only to study participants who have provided written consent. Participants will be instructed to store the product at room temperature (15-25°C), in a dry place away from direct sunlight.

*Pasteurized Akkermansia muciniphila MucT*

Pasteurized *Akkermansia muciniphila* will be provided to the sponsor by A-Mansia biotech. Production, packaging and labeling of pAkk will be performed by A-Mansia Biotech.

The sponsor will be responsible for storing pAkk in a proper place, inaccessible to unauthorized persons. The sponsor will be responsible for storing pAkk at the appropriate conditions and inaccessible to unauthorized persons.

The investigator agrees that pAkk will be dispensed only to study participants who have provided written consent. Participants will be instructed to store the product at room temperature (15-25°C), in a dry place away from direct sunlight.

## 7. NON-INVESTIGATIONAL PRODUCT

### 7.1 Name and description of non-investigational product(s)

#### *Fructo-oligosaccharides*

FOS belong to the group of inulin-type fructans (ITFs); water soluble, non-digestible and fermentable carbohydrates. A lot of vegetables contain inulin-like fructans, such as chicory roots, asparagus, onions, bananas and garlic.

These ITFs are  $\beta$ -(2-1)-linked fructans with a terminal  $\alpha$ -linked glucose. Fructo-oligosaccharides have a chain length of  $<10$ .

ITF cannot be digested by humans due to the aforementioned bonds, but can however be fermented by bacteria, such as *Bifidobacterium animalis* subsp. *lactis* and other bifidobacterial species within the human colonic microbiota..

### 7.2 Summary of findings from non-clinical studies

Fructo-oligosaccharides are safe and extensively studied in humans in dosages  $\leq 20$  grams per day. Moreover, it is part of a healthy diet. Therefore, we will only discuss the findings from clinical studies.

### 7.3 Summary of findings from clinical studies

One approach of modifying gut microbiota in adults is by supplementation with fructo-oligosaccharides (FOS), which are also prebiotics. The most recent definition of prebiotics by the International Scientific Association for Pro- and Prebiotics (ISAPP) is “a substrate that is selectively utilized by the host microorganisms conferring a health benefit”. FOS have been recognized as prebiotic by the ISAPP in this recent publication. The European Union (Reg EC No 1169/2011) definition comprises “carbohydrate polymers with three or more monomeric units, which are neither digested nor absorbed in the human small intestine” and again categories are defined. It is noteworthy that FOS prebiotics selectively stimulate certain microbiota species, while not all dietary fibres show prebiotic properties. FOS, besides being prebiotic, is also a dietary fibre.

As previously stated, FOS is safe and widely used by the food industry globally to enhance fibre in foods. It has been extensively studied in humans in dosages  $\leq 20$  grams a day whereby addition of FOS increased the abundance of *Bifidobacterium* in the gut microbiota. The increase of *Bifidobacterium* seems dose-dependent, and significantly increasing from doses of 2.5-5 grams per day. In addition, a Belgium study found that liver histology improved in NAFLD-patients when treated with FOS. Further data on ITFs in NAFLD-

patients is predominantly researched in the combination with probiotics, and in combination indirectly shows attenuation of contributing factors of NAFLD.

The adverse effects of fructo-oligosaccharides are in decreasing order excess flatus, bloating, borborygmi, and in minor extent, mild abdominal pain. Although smaller studies describe a dose-dependent effect, with dosages above 5 grams a day increasing frequency and intensity of symptoms, this is not seen in larger sample sizes. Serious adverse events are not reported.

#### **7.4 Description and justification of route of administration and dosage**

Inasmuch as FOS has to be fermented in the intestines, we will give it orally. It will be delivered in sachets (or tubs with scoops), which participants can dissolve in their (non-acidic) drinks, such as water, tea or coffee or sprinkled or mixed in foods such as breakfast cereal, porridge or yoghurt.

#### **7.5 Dosages, dosage modifications and method of administration**

We will give 5 grams of FOS (powder) once per day in the morning, to be taken orally (can be easily dissolved in liquid as highly soluble or mixed in foods).

#### **7.6 Preparation and labelling of Non Investigational Medicinal Product**

The Frutalose® OFP powder will be supplied by Sensus, Roosendaal, in a 40 or 60 kg bag with a Certificate of Analysis to UAMC or the co-packer of choice for packing into sachets or tubs with scoops. Information will be provided by Sensus to facilitate the packing and labelling process as required.

- Product name: Frutalose® OFP
- Product Sponsor: Sensus BV provides the oligofructose as a gift to UMCA.
- Product Manufacturer: Sensus BV and co-packer (for tubs/ sachets)
- Active compound: oligofructose (fructo-oligosaccharides or oligo-saccharides)
- Formulation: Frutalose® OFP contains  $92 \pm 2\%$  oligofructose. Oligofructose is a polydisperse mixture of linear fructose polymers partly ended by a glucose molecule, coupled by means of  $\beta(2-1)$  bonds; it comprises a polydisperse mixture of linear fructose oligomers with degree of polymerization ranging between 2 and 10 units.
- Powder of 5 g sachet to be ingested at same time daily after sprinkling on or mixed in foods (e.g. breakfast cereal/ porridge/ yoghurt) or drinks (e.g. coffee/ tea). Fresh orange juice is possible too provided immediately consumed after mixing. Soft drinks are not suitable due to very low pH. Powder will be delivered in sachets or in containers with a 5 gram scoop.

- If the participant misses a dose in the morning, they can continue to take the missed dose later in the day (before meal). Participants should resume the normal instruction on the following day and missed doses should not be moved to the following day.

### **7.7 Drug accountability**

Study product Fructose® OFP will be stored in a secure area with restricted access. The investigator agrees that the study product will be dispensed only to study subjects who have provided written consent. Compliance will be monitored by return of unused study product. Study participants will be instructed to store the sachets (or tubs with lids tightly shut) at room temperature away from moisture and direct sunlight. At the end of the study for each study participant, left over study products will be collected by the researchers for compliance and for destruction.

## 8. METHODS

### 8.1 Study parameters/endpoints

#### 8.1.1 Main study parameter/endpoint

#### 8.1.2 Primary outcome

To demonstrate that *A. soehngenii* combined with pasteurized *A. muciniphila* and *B. animalis* subsp. *lactis*, FOS and conditioned vegan FMT reduces NASH as defined by an improvement of liver histology in individuals with NASH and fibrosis stage 0-3, with improvement defined as reduction of steatohepatitis by  $\geq 1$  SAF-A point and no worsening of liver fibrosis, or improvement in  $\geq 1$  stage liver fibrosis and no worsening of steatohepatitis.

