**Study population:**

Patients between age 18-75 years with biopsy-proven NASH obtained up to 32 weeks before screening based on tandem reading of two expert liver pathologists: SAF Steatosis score  $\geq 1$ , Activity  $\geq 2$ , Fibrosis  $< 4$ ; 50% of participants should at least have NASH fibrosis stage 1, 2 or 3 according to the NASH CRN fibrosis staging system.

Exclusion criteria are: Current or history of significant alcohol consumption for a period of more than 3 consecutive months within 1 year before screening (significant alcohol consumption is defined as more than 2 units/day for females and more than 3 international units/day for males, on average; 1 international unit contains  $\pm 14$  grams of alcohol), liver cirrhosis or hepatocellular carcinoma, hepatitis B and/or C, auto-immune hepatitis, Wilson's disease, primary sclerosing cholangitis, primary biliary cholangitis, alpha-1-antitripsine deficiency and hemochromatosis, history of liver transplant, current placement on a liver transplant list, use of pre-, pro- or synbiotics, use of systemic antibiotics 3 month prior to randomization, use of tamoxifen, methotrexate or amiodarone, prior or planned bariatric surgery, diabetes mellitus with active GLP-1 receptor agonist treatment, bleeding disorder, International normalized ratio (INR) of prothrombin time  $> 1.4$  or platelet count  $< 50 \times 10^9/L$  at screening, anti-platelet/coagulant therapy use which cannot be temporarily discontinued, any major cardiovascular event within 6 months prior to screening (e.g. myocardial infarction, cerebrovascular accident), prolonged compromised immunity (e.g. recent cytotoxic chemotherapy, HIV-infection with a CD4 count  $< 240$ ), active or prior history of invasive malignancy (except for curatively treated in situ carcinomas [e.g., cervix] or non-melanoma skin cancer) unless a complete remission was achieved, surgery scheduled for the trial duration period, except for minor surgical procedures in the opinion of the investigator, pregnant or nursing women, any condition which, in the investigator's opinion, might jeopardize participants' safety or compliance with the protocol, and participation in another concomitant clinical trial.

A total of 48 patients will receive synbiotic treatment with *A. soehngenii*, pasteurized *A. muciniphila*, *B. animalis* subsp. *lactis* and fructo-oligosaccharides, and will be randomized 1:1

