## 2. OBJECTIVES

### Primary objective

To investigate the therapeutic potential of *A. soehngenii* and pasteurized *A. muciniphila* combined with *B. animalis* subsp. *lactis* and FOS with and without conditioned vegan Lyophilized fecal microbiota transplantation (LFMT) capsules to reduce NASH in patients with fibrotic NASH.

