Throughout the study period, the participants will, in addition to the LFMT or placebo capsules, take the 3 bacterial strains in the morning combined with FOS. They will further be asked to retain their usual dietary habits during the study and to keep a nutritional diary from week -1 to 24 to monitor caloric intake including total calories, dietary carbohydrates, fat, proteins, and fibers. Blood pressure, body weight, and changes in health status will be documented.

Interventions: From the day of the first LFMT capsules until completion of the study, all participants will receive an oral daily dose of 5 grams of fructo-oligosaccharides [Sensus, Roosendaal]. Subsequently, participants will be randomized to receive lean donor LFMT or placebo capsules. This consists of 21 capsules at the first 3 study visits, and a daily ingestion of 2 capsules during the duration of the study (24 weeks). Placebo capsules will consist of saline with a brown pigment. During the 24 week study duration, all participants will also daily take  $10^9$  *A. soehngenii* CH-106 cells (dosage based on previous studies and safety study; provided by Caelus Health),  $10^{10}$  *B. animalis* subsp. *lactis* BLC1 (commercially available Sacco SRL) and  $3 \times 10^{10}$  pasteurized *A. muciniphila* cells (provided by A-Mansia Biotech), and 5 grams of FOS. We have previously observed that gut microbiota composition in the recipient is affected up to 8-12 weeks after donor FMT, so this time window ensures a stable donor gut microbiota composition during the study. The fecal donor samples will be collected, lyophilized ('freeze-dried'), encapsulated and stored at -80°C (see also paragraph 6.8). At home, participants will store the LFMT capsules in the freezer (-20°C). See figure 6 below.

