## SYNCH trial

|               |                                                                                                                                     |
|---------------|-------------------------------------------------------------------------------------------------------------------------------------|
| Participants: | 18 – 75 years with fibrotic NASH (NAS $\geq 3$ , NASH F1-F3 $\geq 50\%$ , F0 $\leq 50\%$ )                                          |
| Arm 1:        | n = 24 receive vegan LFMT-capsules + A. soehngenii , B. animalis subsp. lactis and A. muciniphila       |
| Arm 2:        | n = 24 receive placebo-capsules (saline) + A. soehngenii , B. animalis subsp. lactis and A. muciniphila |

[figure not shown]

Figure 6: Study protocol

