#### 8.1.3 Secondary outcomes

##### Secondary outcomes

To demonstrate that the combined treatment improves:

- non-invasive outcomes of NAFLD, i.e. multiparametric MRI of liver and surrounding subcutaneous adipose tissue (MRI-PDFF, MR elastography, corrected T1), FibroScan Elastography and Controlled Attenuation Parameters, and plasma panel Enhanced Liver Fibrosis (ELF) panel, pro-C3.
- change in blood markers from baseline to end of treatment, namely: liver enzymes (i.e. alanine amino transferase (ALT), aspartate amino transferase (AST), gamma glutamyl transferase (GGT), alkaline phosphatase (ALP)), inflammatory blood markers (i.e. leukocytes, monocytes, CRP, IL-1( $\beta$ ), IL-6, IL-11, IL-17, IL-32, TNF- $\alpha$ , IFN- $\gamma$ , additional markers of inflammatory pathways), SCFA (i.e. propionate, butyrate, acetate), lactate, ethanol, plasma lipids (i.e. LDL, HDL, triglycerides, total cholesterol), FGF-21, adiponectin, leptin, lipopolysaccharides, zonulin, estrogen, vitamin B12, folate acid, other metabolomic and lipodomic outcomes.
- microbiome read outs (composition, engraftment, strain tracking) en metabolites, fecal SCFA-composition, and fecal albumine
- glycemic control, insulin resistance, body weight/BMI, waist circumference and percentage body fat
- MetSy criteria / %
- SCFA production and GLP1 gene and protein expression indicating GLP-1 production
- liver gene expression profile: lipogenic, inflammatory and fibrogenic pathways
- liver pathology, histopathological features, immunofluorescence and assessment of pathophysiological proteins

- NAFLD histology as assessed with a deep-learned algorithm scoring whole slide images of liver biopsies.
- 
- Continuous glucose monitoring (4x 7 consecutive days)
- quality of life (general (SF36) and NAFLD/NASH-specific (CDLQ-NAFLD)).

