### **8.2 Randomisation, blinding and treatment allocation**

Double blind, 1:1 to receive synbiotic treatment in combination with LFMT capsules or placebo. Groups will be stratified by proton-pump inhibitor use, metformin use, and histopathological fibrosis score.

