### **11.3 Benefits and risks assessment, group relatedness**

#### *Benefits*

NAFLD and NASH have an enormous and increasing prevalence: 20-30% of the global population has NAFLD to some extent. NAFLD-related livercirrosis is a growing indication for liver transplantation and the incidence of NASH-related hepatocellular carcinoma is

increasing. The disease progresses slowly and NASH-liver fibrosis is strongly associated with atherosclerotic cardiovascular disease and liver-related and overall mortality. Nevertheless, there is no registered or proven treatment for progressed stages of NAFLD-NASH.

As previously stated, extensive prior research associates the gut microbiome with NAFLD-NASH. Regardless, these studies did not entail a treatment targeting the microbiome to reduce NAFLD-NASH, which would be a big step in the field. Based on available literature on treatment with synbiotics in NAFLD/NASH-patients and our pilot study on FMT in NAFLD/NASH-patients, this trial with adequate sample size endeavours to study if modification of the gut microbiome can attenuate NASH and liver fibrosis.

The benefits the study entails will be discussed in three sections. First, we expect a short term benefit for participants. Our underpowered study in which we administered FMT in NAFLD, showed a trend to reduction of necro-inflammation (i.e. inflammation and ballooning) in histopathological examination. Inflammation and ballooning are the most important predictors of progression of NAFLD-NASH, and subsequent secondary complications. The current study will use LFMT capsules instead of fresh FMT per nasoduodenal tube. This will strongly reduce the burden on participants and will more closely resemble a realistic treatment for NASH. Moreover, recent studies show that LFMT capsules have the same efficacy and show a similar shift of the microbiota composition towards a donor profile, indicating similar engraftment. Half of the individuals will receive the LFMT capsules, and we expect that this already will attenuate NASH. All participants will, in addition, be treated with a complementary synbiotic combination. Multiple small clinical trials already showed a beneficial effect of synbiotics on NAFLD-NASH, without entailing serious side effects. Therefore, we expect a beneficial effect of the synbiotics in both study arms.

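### The primary and secondary outcomes credit the whole combination, but both arms receive the synbiotic, so under randomised control only the added effect of LFMT is identified

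*Protocol*

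**What the plan says.** Section 8.1.2, repeated in the Summary, sets out to demonstrate that the three strains together with "FOS and conditioned vegan FMT reduces NASH as defined by an improvement of liver histology in individuals with NASH and fibrosis stage 0-3". It names no comparator. Section 8.1.3 and the Summary open the secondary outcomes with "To demonstrate that the combined treatment improves".

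The allocation is described differently:

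- Summary, Study population: "A total of 48 patients will receive synbiotic treatment with" the three strains and FOS, followed by 1:1 randomisation to FMT or placebo.
- Section 3: "all participants will receive an oral daily dose of 5 grams of fructo-oligosaccharides".
- Section 3, design box: Arm 2 reads "n = 24 receive placebo-capsules (saline", and the same three strains are listed as for Arm 1.
- Section 8.2: "Double blind, 1:1 to receive synbiotic treatment in combination with LFMT capsules or placebo".

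Three other places bear on the point. Section 11.3 states: "Therefore, we expect a beneficial effect of the synbiotics in both study arms". Section 4.4 sets the target as a 25% reduction after donor FMT combined with the synbiotic, and says the additional potential benefit of the synbiotic was taken into account. Section 10 places the primary analysis between baseline and endpoint, using a two-tailed one-sample t-test or a chi-square test.

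**The concern.** The stated aim and the randomised contrast answer different questions. A claim that the full combination reduces NASH needs a comparison with patients who receive none of it, and the trial has no such arm. The only route from these data to that claim is change from baseline within an arm. Section 10 points that way for the primary analysis.

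Patients enter on a thresholded histology score (Activity of at least 2, section 4.2), so some apparent improvement is expected at the second biopsy without any treatment effect. The null case is the more serious one. If the synbiotic works in both arms, as the sponsor expects, the arms can look alike while the combination is effective, and the stated outcome would invite the reading that it failed. The sample size has the same problem, because it counts a benefit that the between-arm comparison cannot see.

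**Working it through.** **What is identified.** Write m for the mean response over 24 weeks with no study treatment (natural change, regression to the mean, biopsy and reading variability, trial participation). Write S for the synbiotic effect and L for the effect of LFMT given the synbiotic.

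- Arm 1 (LFMT + synbiotic): m + S + L
- Arm 2 (placebo capsules + synbiotic): m + S
- Arm 1 minus Arm 2: L
- Combination versus no treatment: S + L

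Two arm means cannot separate three unknowns. Randomisation delivers L. The quantity credited in section 8.1.2, read as the effect of the combination, is S + L. The change within Arm 1 gives m + S + L, so it equals S + L only if m = 0, and no arm allows m to be checked.

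**The plan's own figure.** Section 4.4 gives 24 per arm for alpha 0.05, power 0.80 and a 25% reduction. It gives no control rate, SD or sidedness, and does not say whether the reduction is absolute or relative. The figure therefore cannot be reproduced from its own inputs. For two proportions with a 25-point difference, two-sided:

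n per arm = [1.960·√(2·p̄·(1−p̄)) + 0.842·√(p1(1−p1) + p2(1−p2))]² / 0.25²

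- 0% vs 25%: 27 per arm; power at 24 per arm is 76%
- 20% vs 45%: 54 per arm; power 45%
- 37.5% vs 62.5%: 62 per arm; power 41%

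One-sided without continuity correction, 24 per arm is reached at 2% vs 27%. For two means, 24 per arm corresponds to a standardised difference of (1.960 + 0.842)·√(2/24) = 0.809, that is an SD of 25/0.809 = 30.9 points. The missing inputs are a separate matter and are shown only to fix a starting point.

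**What the shared benefit does to power (assumptions, not protocol figures).** Grant 80% power for a 25-point combined effect on a continuous scale, SD 30.9, and let the synbiotic supply a share s of it. The between-arm difference is 25·(1−s), with standard error 30.9·√(2/24) = 8.92. Power = Φ(difference/8.92 − 1.960).

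| Share s | Difference | Difference/8.92 | Power |
|---|---|---|---|
| 0 | 25 | 2.80 | 80% |
| 25% | 18.75 | 2.10 | 56% |
| 50% | 12.5 | 1.40 | 29% |
| 75% | 6.25 | 0.70 | 10% |

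The endpoint in section 8.1.2 is a responder definition. Take an assumed untreated response of 20% and 45% on the combination. The control arm becomes 20%, 26.25%, 32.5% or 38.75% for s = 0, 25%, 50% or 75%. Using power = Φ{[difference·√24 − 1.960·√(2·p̄·(1−p̄))] / √(p1(1−p1) + p2(1−p2))}, the results are 45%, 27%, 14% and 6%.

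**The case against.** The protocol does state the contrast correctly in several places. Section 8.2 and the design box set it out openly. The objectives speak of the synbiotic with and without LFMT, which describes the two arms. Section 8.3 says the 24-week biopsy examines the effect of the FMT and compares gene expression by allocation. Section 10 also seeks features that change differently between the groups, and its fallback test, Mann-Whitney, is a two-group test. Adding a treatment to an active background is a legitimate design. All of this stands, and no new arm is called for. But the outcome statements drop the comparator, and sections 4.4 and 10 follow the broader claim, so the inconsistency goes beyond loose phrasing. A SAP could name the test, but it could not supply a comparator without the synbiotic.

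A reader might go further in three ways, none of which the document supports:

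- *The combination is untested.* It is Arm 1, tested against an active background. If the synbiotic does no harm (S ≥ 0), a positive L implies a positive S + L, so a positive trial would support the combination under that assumption. The null case is the one exposed to misreading.
- *The combined effect is not estimable at all.* Before-after change gives an estimate. What it lacks is randomised control.
- *A specific spurious response rate can be quoted.* The protocol gives no reading-error rate, two pathologists read in tandem, and the endpoint also has fibrosis conditions. Any such figure would reflect the assumptions chosen.

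Section 2 refers to "capsules to reduce NASH in patients with fibrotic NASH" while stage 0 is allowed. That is a separate, minor label inconsistency and adds no weight here.

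**Conclusion.** The point holds. As written, the outcomes claim the effect of the full combination, while randomisation identifies only the LFMT increment over synbiotic plus placebo capsules. This rests on the allocation text alone and needs no numerical assumption. The consequence for a null result rests on the sponsor's own expectation that the synbiotic works in both arms. The loss of power is real in direction if that expectation is met and if the 25% includes synbiotic benefit, as section 4.4 indicates. Its size is unknown, because the document gives neither the synbiotic's share nor a control rate or SD. The illustrated falls, from 80% to between 56% and 10% (continuous) or from 45% to between 27% and 6% (binary), depend on the assumed shares of 25% to 75% and the other inputs shown. The matter should be corrected; it does not invalidate the design.

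**What to change.** 1. Reword sections 8.1.2, 8.1.3 and 2 and the Summary. The primary outcome becomes the between-arm difference, LFMT plus synbiotic versus placebo capsules plus synbiotic, in the proportion with histological improvement at 24 weeks in NASH with fibrosis stage 0-3. Frame the secondary outcomes as the same contrast.
2. In section 10, make that between-arm comparison the primary analysis and label within-arm changes from baseline as descriptive.
3. In section 4.4, state the detectable effect as the LFMT increment, without crediting synbiotic benefit that both arms share, and restate the power with the control-arm response rate it assumes.
4. State that the effect of the synbiotic, or of the combination against no treatment, is not estimable with randomised control.

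The cost is a wording amendment, a narrower claim and possibly a less favourable stated power. Arms, treatments and visits are unchanged. If the sponsor wanted 80% power for the increment, the continuous illustration would scale the sample as 24/(1−s)² per arm: about 43 for s = 25% (24/0.5625) and 96 for s = 50% (24/0.25). The alternative is to keep 48 patients and report the lower power openly.
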